### 2.4. Data Monitoring

Due to the nature of the trial (small number of healthy volunteers and short study duration), there is no data monitoring committee. Monitoring of the study is conducted by a risk-based approach. The principal investigator has assessed the level of monitoring using a three-tier scale, placing the study in the medium-risk category based on risk-based evaluation. This assessment considers the investigational product/placebo, the duration and nature of the intervention, as well as the number and characteristics of the study subjects. Level 2 monitoring includes the informed consent process, the investigator’s study file, serious adverse events, subject discontinuations and withdrawals, inclusion and exclusion criteria, and evaluation and verification of the primary endpoints on a per-subject basis. The proper management and handling of the investigational product/placebo are also verified. In addition, source data verification (SDV) is performed 100% for the first two subjects and thereafter for every third subject. The monitoring also includes a site initiation visit before the start of the study and a close-out visit after the final study visit. Other monitoring visits are conducted at least every four months. The monitor ensures that the rights and well-being of the subjects are protected, that written informed consent has been obtained from all subjects prior to participation, that the study is conducted in accordance with the approved protocol and applicable regulations, and that the collected study data are accurate and complete. If the monitor identifies any deviations from the study protocol, procedures, GCP, or applicable regulations, they will promptly report these to the study sponsor and the principal investigator and aim to prevent recurrence of the deviations. The study monitoring is conducted by a trained monitor external to the research groups involved in the trial. Monitoring visits are recorded in the monitoring log form, and reports of the visits are submitted to the principal investigator. Subjects are provided with sufficient information about the monitoring, both in the subject information sheet and verbally. The subject’s personal data protection may be compromised, as the regulatory authority (the Finnish medicines agency Fimea) has the right to access patient records during inspections.

### 2.5. Adverse Event Reporting and Harms

Adverse events related to the study are monitored by actively inquiring about them during study visits, as well as by reviewing laboratory test results and physiological measurements. Study subjects have the opportunity to report adverse events to the principal investigator around the clock via phone and email. Adverse events and side effects will be recorded, and all adverse reactions will be reported annually to Fimea via secure email. At the same time, a summary of the overall safety of individuals participating in the clinical trial will be submitted. All serious adverse events, except for pulmonary embolism, are considered Suspected Unexpected Serious Adverse Reactions (SUSARs) and must be reported to Fimea as soon as possible, but no later than within 7 days. Any updates to the initial report must be submitted within 8 days of the first notification. These reports will be sent via secure email to Fimea. Fimea will forward the information to EudraVigilance on behalf of the principal investigator. SUSARs that are not life-threatening or fatal must be reported within 15 days. Additionally, a summary of the study results must be submitted to Fimea no later than one year after the study has concluded.

### 2.6. Confidentiality

The research nurses and study physicians participating in the study are well-versed in the principles and practices of GCP. All collected data and samples will be processed using pseudonymized coding; individual data cannot be identified from any publications related to the study. The research data will be handled in accordance with the data protection policies of Oulu University Hospital and the University of Oulu, in compliance with European GDPR legislation. Only researchers involved in the study will have access to the research data, and they are bound by confidentiality.

## 3. Procedure

### 3.1. Recruitment

Recruitment will primarily be based on an announcement distributed via email lists of the Oulu Medical Guild and the Oulu Dental Guild at the Faculty of Medicine, University of Oulu. If necessary, individuals other than medical and dental students may also be recruited; newspaper advertisements will not be used.

### 3.2. Implementation

Individuals who respond to the recruitment announcement will be interviewed by phone using a structured interview form by an investigator. If no concerns arise during the interview regarding eligibility for the study, an appointment will be scheduled for the screening visit. Based on these measurements and assessments, the study physician makes the final decision regarding the individual’s eligibility for participation. The study schedule is reviewed with the individual, and an appointment for the first study visit is booked.

### 3.3. Intervention Description

Study Day 1:
Female participants undergo a urine pregnancy test (Apteekkarin pregnancy test, CE-marked). In case the result is positive, participation in the study is discontinued.Weight, height and waist and hip circumference are measured using a scale (Seca Model 861, Seca GmbH, Hamburg, Germany), stadiometer (Seca), and measuring tape, respectively.Blood pressure and pulse are measured using an arm cuff monitor (GE CARESCAPE Dinamap V100, GE Healthcare, Chicago, IL, USA).Study medication (either placebo or roxadustat capsules, blinded and provided by the hospital pharmacy) is dispensed. The first dose is taken under supervision during the visit; the subsequent doses are taken independently at home on study days 3, 5, and 8.
○Participants record each dose of medication taken in a diary provided during the Day 1 visit and return the empty medication packages at the final visit of the study arm.

Study Day 9 (Morning, participant fasted for 10–12 h):Weight, waist and hip circumference are measured on Study Day 1.Blood pressure and pulse are measured on Study Day 1.Fasting blood samples are collected for the following analyses in the clinical laboratory (NordLab) of the Oulu University Hospital, and results are shared with participants: CBC with Differential, E-Reticulocytes, plasma Potassium, Sodium, Creatinine, ALT, AST, Bilirubin, ALP, gamma-GT, Albumin, TSH, Total Cholesterol, LDL, HDL, Triglycerides, hsCRP, HbA1c, lp(a). Additional analyses may be performed in academic or commercial labs.Additional blood samples (2 × 8 mL) are collected in CPT tubes (BD Biosciences, San Jose, CA, USA) for isolation of mononuclear cells and RNA extraction (RNeasy Mini Kit, Qiagen, Hilden, Germany) to study gene expression related to HIF response and drug metabolism. DNA is also extracted from the blood sample, enabling the potential to investigate genes that could be involved in glucose, lipid, hormone, bone, and drug metabolism, or blood pressure regulation.Serum and plasma samples (10 mL each; plasma with EDTA) are stored for potential additional analyses related to metabolism, including serum metabolomics and plasma 4β-hydroxycholesterol levels. If the participant withdraws, these samples will be destroyed.After blood sampling, a 2 h OGTT is performed. The participant drinks a solution containing 75 g of glucose. Venous blood samples are taken at 0, 30, 60, and 120 min to measure glucose, insulin, and C-peptide in Nordlab. These results are shared with the participants. At each time point, 2 × 5 mL blood samples are collected, immediately treated with a dipeptidyl peptidase IV (DPP) inhibitor, and used for glucagon, GLP-1 and GIP assays by ELISA at the Faculty of Biochemistry and Molecular Medicine, University of Oulu. One sample is stored for potential further analyses.Participants are instructed in the use of an ambulatory blood pressure monitor (Mobil-O-Graph, IEM GmbH, Aachen, Germany), which is worn for 24 h at home. Data is analysed using HMS-CS Hypertension Management Software, version 6.3 (IEM) [22].

Study Day 10 (Afternoon):
Participant returns the ambulatory blood pressure monitor.Body composition measurements:
○Bioimpedance technique is used to measure lean mass, soft tissue mass, fat mass, total body water, and visceral fat by the InBody 720 device (InBody Co., Ltd., Seoul, Republic of Korea).○Skinfold thickness is measured from the thigh and arm (near-infrared spectroscopy [NIRS] sensor area) using a Harpenden calliper (Baty International, UK).
Autonomic nervous system regulation assessment:
○Heart rate variability, blood pressure variability, and respiratory rate are measured at rest in a seated position for 5 min:
▪ECG: 3-channel ECG (MAC 5500 HD, GE Healthcare, Chicago, IL, USA)▪Blood pressure: Non-invasive finger cuff (Nexfin, BMEYE Medical Systems, Amsterdam, The Netherlands)▪Respiratory rate: PneumoTrace (ADInstruments, Sydney, Australia) [23]

Assessment of microcirculation:
○A NIRS device (Oxymon MK III, Artinis Medical Systems, Elst, The Netherlands), assessing changes in oxyhaemoglobin, deoxyhaemoglobin, total haemoglobin, and tissue saturation index (TSI), is used to measure skeletal muscle microcirculation non-invasively at rest and during occlusion [24,25].○Measurements are taken at rest (1 min), during occlusion (5 min), and recovery (3 min) from the forearm (*M. flexor digitorum superficialis*).○Occlusion is performed using a rapid-inflation cuff (Hokanson model E20, Hokanson, Inc., Bellevue, WA, USA) on the left arm.○A skin map is drawn based on skin markings to ensure consistent measurement location in the second study arm.Maximal exercise test (VO_2_max):
○Conducted using a cycle ergometer (Monark Ergomedic 839E, Vansbro, Sweden) starting at 40 W with ramp protocol (men: +20 W/min, women: +15 W/min), and gas exchange was monitored (Vyntus™ CPX, Vyaire Medical, Chicago, IL, USA)○Measurements during rest, exercise, and recovery include blood pressure, 15-lead ECG, heart rate, blood lactate, and muscle microcirculation:
▪Blood pressure: Measured at rest, during each load stage, and post-exercise (2, 5 min and 10 min) using an arm cuff (Schiller BP-200-plus, Schiller, Doral, FL, USA; Korotkoff sound analysis with QRS trigger).▪ECG: Continuous 15-lead ECG (CAM-14; GE Healthcare, Dusseldorf, Germany).▪Heart rate: Monitored continuously using Polar Verity Sense and Polar H10 chest strap (Polar Electro, Kempele, Finland).▪Blood lactate: Measured from fingertip using Lactate Scout+ metre (SensLab/EKF Diagnostics, Leipzig, Germany) at rest, every 2 min during exercise, and post-exercise (5 min and 10 min).▪Microcirculation: Continuously measured using NIRS (Artinis Medical Systems, The Netherlands) from the outer thigh muscle (*M. vastus lateralis*).

The flow diagram and participant flow chart are described in Figure 1, and the schedule of enrolment, interventions and assessments in Figure 2.

## 4. Expected Results

### 4.1. Primary and Secondary Outcomes

The primary outcome is the change in plasma total cholesterol levels. The secondary outcomes are changes in plasma LDL cholesterol and triglycerides levels, insulin resistance and glucose tolerance in a 2 h OGTT, 24 h blood pressure, exercise tolerance and autonomic regulation of cardiovascular function, skeletal muscle microcirculation and body composition. All measurements will be conducted during both study arms. Results obtained during the study arm in which participants receive roxadustat will be compared to the results from the placebo arm. Participants will serve as their own controls.

### 4.2. Statistical Analyses

Statistical analyses will be mostly conducted using Student’s paired (dependent samples) *t*-test, as each participant serves as their own control in a crossover study design, and the long interval between study arms is assumed to eliminate any sequence effect. The normality of the measured variables will be assessed. If a variable is not normally distributed, a logarithmic transformation will be applied prior to statistical analysis, or non-parametric tests will be used. For multivariable analyses, regression models will be employed as the statistical method. Principal component analysis will be used to account for multiple testing when necessary. Sensitivity analyses on potential period or carry-over effects will be conducted.

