## 2. Experimental Design

### 2.1. Trial Design

The study is double-blind, placebo-controlled, and crossover in design. It consists of two 10-day study arms separated by a washout period of at least 4 weeks. The study plan involves recruiting 24 healthy volunteers and administering 70 mg of roxadustat orally (Evrenzo 70 mg, Astellas Pharma (Tokio, Japan), encapsulated in a white capsule) thrice a week over a 10-day period (a total of 4 doses). The effects will be compared to a matched placebo arm, during which participants will receive white placebo capsules thrice a week. Participants are randomised to a treatment sequence. Half of the participants will be randomised to receive roxadustat during study arm 1 and placebo during arm 2, while the other half will receive placebo in arm 1 and roxadustat in arm 2. The randomization will be conducted by the hospital pharmacy of Oulu University Hospital, which holds the randomization code. The code will be unblinded at the end of the study, at which point the pharmacy will provide the allocation information to the principal investigator. At the end of each study arm, participants will undergo blood sampling, a 2 h OGTT, 24 h ambulatory blood pressure monitoring, anthropometric and body composition measurements, heart rate variability assessment, skeletal muscle microcirculation measurement, and a maximal exercise test.

The study will be conducted at the Research Unit of Internal Medicine in the Oulu University Hospital, Oulu, Finland, the Physiology Research Laboratory in the Research Unit of Biomedicine and Internal Medicine, Faculty of Medicine, University of Oulu, and the Faculty of Biochemistry and Molecular Medicine, University of Oulu.

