#### 2.2.4. Sample Size

A total of 24 healthy volunteers will be recruited for the study. If any participants discontinue, new individuals will be recruited to ensure the final sample size remains at 24. The hospital pharmacy will assign the same treatment sequence to the replacement participant as was assigned to the one who withdrew. Data collected from participants who discontinue will not be used. With this sample size, the study has a 95% probability (power) of detecting a 0.3-unit (mmol/L) change in plasma total cholesterol levels at a two-sided significance level of 0.05, assuming a standard deviation (SD) of 0.38 mmol/L for the change in the primary outcome. The assumptions for this power calculation are based on a previous clinical trial evaluating the efficacy of roxadustat, in which a 3-wk treatment reduced plasma total cholesterol by 0.9 mmol/L more in CKD-ND patients (*n* = 82–84) compared to those treated with placebo (*n* = 43), with the between-group difference remaining consistent for up to nine weeks after treatment initiation [3].

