### 2.3. Blinding and Randomization

The study is double-blind. Trial participants, care providers and outcome assessors will be blinded during the data collection. Randomization will be performed for the treatment sequence, and it is managed by the hospital pharmacy at Oulu University Hospital, which holds the randomization code. Half of the participants will be randomised to receive roxadustat during study arm 1 and placebo during arm 2, while the other half will receive placebo during arm 1 and roxadustat during arm 2. The pharmacy delivers the drugs in envelopes having the participant number (1–24) and study arm (1 or 2) to the research centre, where they are kept at room temperature in a locked cabinet. Any unused drugs are returned to the pharmacy, which is responsible for disposal. Both the study medicine (Roxadustat, Evrenzo 70 mg) and the placebo are packed in similar, white-coloured capsules. The code will be blinded until the end of the study (i.e., until 24 participants have completed two study arms), at which point the pharmacy will provide the allocation information to the principal investigator. In case of serious adverse events or pregnancy, the randomization code will be unblinded immediately.

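### The main paired t-test leaves period out for a reason that covers only carry-over; the estimate stays unbiased, but a common period shift would cost power and precision

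*Protocol article*

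**What the plan says.** Section 4.2 of the protocol article states: "Statistical analyses will be mostly conducted using Student’s paired (dependent samples) *t*-test". It gives two grounds. Each participant is their own control, and "the long interval between study arms is assumed to eliminate any sequence effect". No other test is named for the primary outcome, plasma total cholesterol. Period comes in at the end of the same section: "Sensitivity analyses on potential period or carry-over effects will be conducted".

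The design behind this is in three other places:

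- Section 2.1: "It consists of two 10-day study arms separated by a washout period of at least 4 weeks". The gap has a minimum and no stated maximum.
- Section 2.3: "Half of the participants will be randomised to receive roxadustat during study arm 1 and placebo during arm 2", and the other half in the reverse order, which gives 12 per sequence.
- Section 2.2.4: after a withdrawal "new individuals will be recruited to ensure the final sample size remains at 24", and "The hospital pharmacy will assign the same treatment sequence to the replacement participant as was assigned to the one who withdrew". The power statement there is that "the study has a 95% probability (power) of detecting a 0.3-unit (mmol/L) change in plasma total cholesterol levels", at two-sided 0.05 with an SD of the change of 0.38 mmol/L.

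**The concern.** Carry-over and period effects are different things. Carry-over is what the first treatment leaves behind, and a washout can limit it. A period effect is a shift between the first and second measurement occasions that happens whatever was taken. Possible sources are season, changes in diet or activity, assay drift and, for the maximal exercise test, familiarity with the procedure. An interval does not remove such a shift. Section 2.2.3 also lets participants live as usual during the washout, so some drift between arms is possible.

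The reason given in section 4.2 can therefore justify leaving out a carry-over term, but not a period term. Period is known for every value and order is randomised, so the design supports adjustment directly. Without it, a shift common to all participants is counted as random variation between them. At stake are the power of the primary test and the width of its confidence interval.

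**Working it through.** **Inputs.** From section 2.2.4: n = 24, difference 0.30 mmol/L, SD of the within-participant difference 0.38 mmol/L, two-sided alpha 0.05. From sections 2.3 and 2.2.4: 12 per sequence, kept by same-sequence replacement. Assumed: π, the period 2 minus period 1 shift in total cholesterol, common to all participants. The documents give no value, so a range is shown. The SD of 0.38 is first taken as free of any period effect.

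**Step 1: the plan's own figure.** Standard error = 0.38/√24 = 0.0776. Noncentrality = 0.30/0.0776 = 3.87. With 23 degrees of freedom and a critical value of 2.069, the noncentral t distribution gives power of 95.9%. The stated 95% is reproduced; the smallest n that reaches it is 23.

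**Step 2: what a period shift does to the paired test.** The roxadustat-minus-placebo difference has mean δ − π when roxadustat comes first and δ + π when placebo comes first. With 12 in each sequence the overall mean is (12(δ − π) + 12(δ + π))/24 = δ, so there is no bias. The expected sample variance of the 24 differences becomes

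0.38² + π² × 24/23.

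At π = 0.2 this is 0.1444 + 0.0417 = 0.1861, an apparent SD of 0.431.

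The true standard error of the mean is still 0.0776; only its estimate is inflated. Putting the apparent SD into the step 1 formula would therefore understate power (90.3% at π = 0.2). The figures below come instead from simulating the test, with 12 per sequence and 400,000 trials per shift. They carry a simulation error of about 0.1 point.

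| π (mmol/L) | Apparent SD | Power, paired t | Mean 95% CI half-width | True two-sided alpha |
|---|---|---|---|---|
| 0 | 0.380 | 95.9% | 0.159 | 5.0% |
| 0.1 | 0.393 | 95.3% | 0.164 | 4.3% |
| 0.2 | 0.431 | 92.8% | 0.180 | 2.7% |
| 0.3 | 0.488 | 87.7% | 0.204 | 1.3% |
| 0.4 | 0.558 | 78.7% | 0.234 | 0.5% |

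**Step 3: the period-adjusted analysis.** Estimate δ by the average of the two sequence means and take the variance pooled within sequences. The standard error is again 0.38/√24, on 22 degrees of freedom with a critical value of 2.074. Power is 95.85%, against 95.92% for the paired test at π = 0. Across the whole range of π it stays at about 95.9% power, a half-width of 0.159 and an alpha of 5%.

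**Step 4: the other reading of the SD.** If 0.38 already contains a period effect, the stated power stands and adjustment improves on it. With π = 0.1 inside the 0.38, the within-sequence SD is √(0.1444 − 0.01 × 24/23) = 0.366 and adjusted power is 97.0%. With π = 0.2 it is 0.320 and 99.2%.

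**The case against.** The article does not claim that the interval removes period effects. It speaks of a sequence effect and then names period and carry-over separately for sensitivity analysis. Read as carry-over, the sentence is loosely worded but defensible. This stands: period has not been overlooked. What remains is that the stated reason does not support leaving it out of the main test.

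A reader might infer that the primary result would be biased or prone to false positives. The documents do not support that. Same-sequence replacement keeps 12 per sequence, the paired mean is then unbiased, and the true alpha falls below 5%, so a significant result remains valid. Unequal numbers per sequence could arise only where a completer lacks an individual measurement, which mainly concerns secondary outcomes. The bias would then be π times the difference in numbers over their total. For 12 against 9, an illustration with no basis in the documents, that is 3/21 = 0.14π.

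A reader might also infer that the 95% power statement is wrong. It reproduces, and it survives a shift of 0.1 mmol/L, one third of the target difference. The larger losses need shifts close to or above the target difference. Section 2.2.3 asks for stable habits within the arms, which limits such shifts in cholesterol. Familiarity with the exercise test concerns a secondary outcome, and the figures above are for cholesterol.

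A period term also removes only the part of the shift that all participants share. If enrolment is staggered, which the article does not state, seasonal effects would differ between participants and adjustment would recover less.

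Finally, model details often belong in a statistical analysis plan that is not shown. That does not answer this point, because the article itself names the main test, gives the reason for it and puts period in a secondary role.

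**Conclusion.** The point holds as one of efficiency and rationale, not validity. Section 4.2 chooses an unadjusted main test, and its stated reason addresses carry-over only. The loss of power is under one point for a common shift up to 0.1 mmol/L, about 3 points at 0.2, about 8 at 0.3 and about 17 at 0.4. The confidence interval is wider by a factor of 0.180/0.159 = 1.13 at 0.2 and 0.204/0.159 = 1.28 at 0.3.

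These figures rest on an assumed, additive shift common to all participants, on 12 complete pairs per sequence, and on 0.38 being free of a period effect. The planned sensitivity analyses would bring a shift to light, but the headline p-value and interval would still come from the less efficient test. The change is worth making because it costs almost nothing.

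**What to change.** Make the primary analysis, and that of the continuous secondary outcomes, a crossover model with treatment, period and sequence as fixed effects and participant as a random effect. For complete pairs this gives the same treatment comparison as the two-sample t-test on period differences. Keep the unadjusted paired t-test as the sensitivity analysis. Reword the rationale in section 4.2 to say that the washout is assumed to limit carry-over, and drop any suggestion that it deals with the order of treatment as a whole.

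The cost is a change of wording and one degree of freedom: 95.92% to 95.85% power when there is no period effect. No participants, visits or measurements are added. For secondary outcomes with isolated missing values, the period term also guards against the bias that unequal numbers per sequence would bring.
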